### Primary endpoint analyses

The phase II primary endpoint of MRD negativity in each stage of the phase II part of the trial will be assessed once 9 and 23 participants have received at least 4 weeks of obinutuzumab treatment and been followed until 6 months post-randomisation. The phase III primary endpoint of PFS will be assessed once 120 events (progressions/deaths) have been observed overall. A formal interim analysis will be carried out when 60 events have been observed overall in order to allow large differences between the trial arms to be reported early (Fig. 4). PFS is defined as the time from randomisation to first documented evidence of progression or death. Participants not having progressed or died or who are lost to follow-up at the time of the phase III analyses will be censored at the last date they were known to be alive and progression-free. For the analysis of primacy, we will use a Cox proportional hazards model [15] to compare the trial arms, adjusting for the minimisation factors, to calculate the HR and corresponding 95% CIs. The *p* value to assess for statistical significance will be compared with 0.047 to account for the formal interim analysis. In addition, median survival estimates with corresponding 95% CIs, as well as Kaplan-Meier curves [16], will be produced by trial arm.

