### Sample size

The overall sample size of the trial is powered for the phase III primary endpoint of PFS. An internal literature review investigating patients who have received up to three lines of previous therapy of any type and who responded to their most recent therapy with at least a PR suggested that 3 years is a reasonable estimate for median PFS in the control population (i.e., no consolidation), which translates to approximately 2 years from the time the participants are randomised (because it will be 3–24 months after previous therapy). An important clinical improvement would be an increase in median PFS from 2 to 3.3 years, a relatively large improvement, because consolidation is given at a time when patients would otherwise be in remission and treatment-free. The trial is powered to test the null hypothesis of no difference in PFS between the treatment arms, with a two-sided 5% level of significance and 80% power. Assuming 3 years of recruitment, 3 years of follow-up and allowing for a 5% drop-out rate, 188 participants are required (94 per arm) in order to observe 120 progression/death events. Losses to follow-up for the primary endpoint are expected to be extremely uncommon due to the short treatment duration and straightforward and regular follow-up schedule. A formal interim analysis on PFS will be carried out and reported to the data monitoring and ethics committee (DMEC) when half the required number of events have been observed (60 events).

The O’Brien and Fleming alpha-spending function [11] will be used to adjust for multiple testing to conserve the overall type I error, which recommends that the interim results be compared with a *p* value of 0.005, and the final analysis results are then compared with a *p* value of 0.047.

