### Randomisation

Following confirmation of eligibility and informed consent, MRD-positive participants will be randomised into the trial by an authorised staff member at the trial research site. Randomisation will be performed centrally using the Leeds Clinical Trials Research Unit (CTRU) automated 24-hour telephone registration and randomisation system. Participants will be randomised on a 1:1 basis to receive either obinutuzumab consolidation or no treatment. Participants will be informed of their treatment allocation in this open study.

A computer-generated minimisation program that incorporates a random element will be used to ensure treatment groups are well-balanced for the following participant characteristics: bone marrow MRD level at entry (≤0.3%, >0.3%), number of lines of previous therapy (one, more than one), age group (≤65, >65 years), sex (male, female), Binet stage of disease prior to most recent CLL therapy (A progressive or B, C) and previous rituximab (yes, no).

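### The primary Cox model leaves out time since last CLL therapy; pre-specifying it is a cheap efficiency gain, about 2 to 4 points of power if the sample-size section's own shift applies to each participant

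*Protocol article*

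**What the plan says.** Primary endpoint analyses (Protocol article) measures PFS from randomisation and compares the arms with a Cox model "adjusting for the minimisation factors, to calculate the HR and corresponding 95% CIs". The p value "will be compared with 0.047 to account for the formal interim analysis".

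Randomisation lists six minimisation factors: marrow MRD level, "number of lines of previous therapy (one, more than one"), age group, sex, Binet stage and earlier rituximab. Time since the last therapy is not one of them, so it is neither balanced by the allocation nor adjusted for.

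Trial population admits patients 3 to 24 months after their last CLL treatment, so the interval has to be established before randomisation. Secondary endpoint analyses uses the end of the most recent therapy as the time origin for comparisons that involve the MRD-negative cohort.

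Sample size takes a control median PFS of 3 years and turns it into about 2 years from randomisation, "because it will be 3–24 months after previous therapy". The target is "an increase in median PFS from 2 to 3.3 years", tested "with a two-sided 5% level of significance and 80% power".

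**The concern.** The clock for PFS starts at randomisation, but participants reach randomisation at very different distances from their last treatment. If PFS were exponential, elapsed time would carry no information and the control median from randomisation would still be 3 years. By cutting it to about 2 years, the sample-size section assumes that a patient further from therapy has less progression-free time left. The primary model then ignores that dependence, although the value is on file.

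At stake is efficiency. In a time-to-event model, leaving out a prognostic baseline value costs some power and leaves chance imbalance in that value within the estimate. The design has little slack: at 120 events and the stated medians, power is already just under 80%.

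**Working it through.** **1. Reproduce the design.** Inputs from Sample size: medians 2 and 3.3 years, two-sided 5%, 80% power, 1:1 allocation, and "188 participants are required (94 per arm) in order to observe 120 progression/death events". Timing: "Assuming 3 years of recruitment, 3 years of follow-up and allowing for a 5% drop-out rate".

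- Hazard ratio under exponential PFS: 2/3.3 = 0.606, so |ln HR| = 0.501.
- Schoenfeld events: 4 × (1.960 + 0.842)² / 0.501² = 126. With the HR rounded to 0.6 the result is 121.
- Power at 120 events: Φ(√120/2 × 0.501 − 1.960) = Φ(0.783) = 78.3%. At HR 0.6 it is 79.9%. At the final level of 0.047 and HR 0.606 it is 77.5%.
- Sample size: uniform accrual over 3 years plus 3 years of follow-up gives event probabilities of 0.780 and 0.605, mean 0.693. Then 120/0.693 = 173.3, rounded up to 174, and 174/0.95 = 184, against 188 stated.

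The plan's figures reproduce within rounding.

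**2. What the 3-to-2-year shift implies.** Read participant by participant, the remaining control median is 36 months minus elapsed time: 33 months (2.75 years) for entry at 3 months and 12 months (1 year) for entry at 24 months. The hazards at the two ends differ by a factor of 2.75. With elapsed time uniform over 3 to 24 months (an assumption), the mean remaining median is 3 − 1.125 = 1.875 years, close to the plan's 2, and the SD of the log hazard is 0.285.

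A second reading keeps one Weibull curve from end of therapy with median 3 years and conditions on being progression-free at entry. The pooled median from randomisation is then 3.0 years at shape 1, 2.34 at shape 1.5, 2.11 at shape 2 and 2.0 at shape 2.49. Only a clearly rising hazard reproduces the plan's step.

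**3. Power with and without the interval.** Simulated trials: 188 participants, 1:1, conditional HR 0.606, analysis at the 120th event, Wald test at 0.047, elapsed time uniform over 3 to 24 months, minimisation factors not included; 4,000 to 10,000 replicates. The standard error of each power is at most about √(0.75 × 0.25/4,000) = 0.7 points. The difference is more precise, because both models are fitted to the same data.

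| Assumed dependence on elapsed time | Without | With | Change (points) |
|---|---|---|---|
| None (exponential) | 77.0% | 76.9% | −0.1 |
| Shift applied to each participant | 73.8% | 76.8% | +3.0 |
| Weibull, shape 1.2 | 77.4% | 76.9% | −0.5 |
| Weibull, shape 1.5 | 76.9% | 77.1% | +0.3 |
| Weibull, shape 2.0 | 75.2% | 77.1% | +1.9 |
| Weibull, shape 2.49 (matches 3 to 2 years) | 73.2% | 77.0% | +3.8 |
| Log-linear, SD of log hazard 0.1 | 76.9% | 77.0% | +0.1 |
| Log-linear, SD 0.2 | 75.9% | 77.1% | +1.2 |
| Log-linear, SD 0.3 | 74.1% | 76.6% | +2.5 |
| Log-linear, SD 0.4 | 71.3% | 77.2% | +5.9 |
| Log-linear, SD 0.5 | 68.2% | 77.1% | +8.8 |

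Changes are taken before rounding. The last row is an extreme: with log hazard linear in a uniform interval, SD 0.5 means a range of 0.5 × √12 = 1.73, or a 5.7-fold hazard difference between entry at 3 and at 24 months.

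**4. With the six factors in both models,** as planned, the shift reading gives about 72.9% without and 75.4% with the interval, a gain of about 2.4 points (2.0 to 2.8 across settings). A weak effect gives about 0.4, and no effect gives essentially no change.

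**5. Hazard ratio.** In those six-factor runs the planned model's mean HR was about 0.60 to 0.61 against a true 0.606.

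**The case against.** The strongest reply is that nothing here is wrong. An intention-to-treat Cox model adjusted for the minimisation factors is conventional and valid, and every trial leaves out some prognostic variable. That stands, and it limits the point to an efficiency suggestion.

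Four further objections also have weight.

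- The sample-size section makes an average change of time origin. It never calls the interval prognostic and gives no participant-level effect. A reader might infer that the plan itself establishes a strong covariate and therefore a definite loss of 2 to 3 points. The document does not support that: the strength is an assumption, and milder Weibull shapes give almost nothing.
- A reader might also infer that the planned hazard ratio is pulled towards 1. Without the six factors the simulated mean HR was 0.616, against 0.604 with the interval added. With the six factors in the model the departure from 0.606 is negligible.
- Chance imbalance in the interval is not bias. Randomisation balances it in expectation, and the confidence interval allows for chance.
- Correlation with marrow MRD or number of lines would shrink the gain, and a long progression-free interval may mark better disease and offset it.

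The last item does not remove the case. A fitted coefficient can take either sign, and a run with the effect reversed gave a similar gain (73.2% to 76.3%). Nor is the point simply left to an unseen analysis plan, because the article states the primary covariate set.

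One inference should be declared: Baseline assessments does not list the interval. That it is held follows from the eligibility window and the secondary time origin.

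**Conclusion.** The point holds as an optional gain in efficiency and precision. It corrects neither bias nor type I error, and the planned test may be used as it stands.

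The primary model omits a baseline value that is known for every randomised participant and on which the plan's own 3-to-2-year step implies remaining PFS depends. Assuming that step applies to each participant and that entry times are uniform over 3 to 24 months, adjustment gains about 2 to 4 points of power: 2.4 with the six factors included, 3.0 without them, and 3.8 under the calibrated Weibull. The range starts at about 0 for a weak or absent effect and goes higher for a stronger one (8.8 at a log-hazard SD of 0.5). If the interval is not prognostic, the largest loss seen was about half a point. The omission is certain; the size is conditional on a strength that the document does not supply.

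**What to change.** In Primary endpoint analyses, and in the analysis plan that the article says will be signed off before any analysis, add months from end of last CLL therapy to randomisation as a pre-specified continuous covariate beside the six minimisation factors. Fix its functional form at the same time.

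The same covariate may be added to the OS and TFS models for consistency. No gain is claimed there, because none was calculated.

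The allocation cannot change, since recruitment closed in February 2017, and it need not. The cost is one sentence, one degree of freedom and, if the interval proves uninformative, at most about half a point of power. No new data should be needed, provided the end-of-therapy date is confirmed as recorded for all randomised participants.

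### The final PFS threshold of 0.047 does not follow from the O'Brien-Fleming method named for it; the stated pair 0.005/0.047 is valid but slightly conservative

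*Protocol article*

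**What the plan says.** The Sample size section of the protocol article sets the PFS comparison "with a two-sided 5% level of significance and 80% power". It plans that "188 participants are required (94 per arm) in order to observe 120 progression/death events", with one formal interim "when half the required number of events have been observed (60 events"). It names the method: the O'Brien "and Fleming alpha-spending function [11] will be used to adjust for multiple testing to conserve the overall type I error". It then gives the levels that this method is said to recommend: the interim is compared with a p "value of 0.005, and the final analysis results are then compared with a" p value of 0.047. The Primary endpoint analyses section repeats the final level for the adjusted Cox model: the p value "to assess for statistical significance will be compared with 0.047 to account for the formal interim analysis".

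**The concern.** The section names a method and prints the two numbers said to come from it. With one interim at half the events and an overall two-sided 5%, that method fixes both levels, and 0.047 is not the final one. This is the decision rule for the phase III primary endpoint. A reader who follows the named method and a reader who follows the printed numbers would apply different thresholds. At the final look they would disagree on p values between 0.047 and about 0.048 or 0.049. At the interim they could disagree between about 0.003 and 0.005, depending on which O'Brien-Fleming version is meant.

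**Working it through.** **Inputs (protocol article, Sample size):** overall two-sided alpha 0.05; one interim at 60 events and the final analysis at 120, so the information fraction is t = 60/120 = 0.5; median PFS 2 against 3.3 years, so the hazard ratio is 2/3.3 = 0.606 if PFS is exponential; 1:1 allocation (Randomisation section).

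**Model.** Under the null, the interim and final statistics Z1 and Z2 are standard bivariate normal with correlation sqrt(0.5) = 0.707. For two-sided nominal levels p1 and p2 with critical values c1 and c2, overall alpha = 1 − P(|Z1| < c1 and |Z2| < c2).

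**The stated pair.** p1 = 0.005 gives c1 = 2.807, and p2 = 0.047 gives c2 = 1.986. Overall alpha = 0.0489. The pair therefore holds the 5% level but does not use all of it.

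**What the named method gives at t = 0.5:**

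| Version | Derivation | Interim | Final |
|---|---|---|---|
| Classical O'Brien-Fleming | c2 = c, c1 = c × sqrt(2); alpha = 0.05 gives c = 1.977, c1 = 2.797 | 0.0052 | 0.0480 |
| Spending function, 2.5% per side | first spend 4 × [1 − Φ(2.2414/sqrt(0.5))]; c1 = 2.963; final level solved for alpha 0.05 | 0.0031 | 0.0490 |
| Spending function on two-sided 5% | first spend 2 × [1 − Φ(1.96/sqrt(0.5))]; c1 = 2.772; final level solved for alpha 0.05 | 0.0056 | 0.0478 |
| Interim fixed at 0.005 | final level solved for alpha 0.05 | 0.0050 | 0.0481 |

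To three decimals the final level is 0.048 or 0.049 in every row. Working backwards, a final level of 0.047 would use the full 5% only with an interim level of 0.0070.

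**Other interim timings.** At t = 0.55 the classical boundary is 0.0075/0.0472 and the per-side spending function gives 0.0050/0.0484. Each reproduces one printed figure and misses the other. No fraction tried between 0.30 and 0.75 gave both.

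**Size of the effect.** Under the design alternative the expected final Z is ln(3.3/2) × sqrt(120/4) = 0.5008 × 5.477 = 2.743. Two-look power at 120 events:

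- stated pair: 77.7%
- classical boundary: 78.0% (difference 0.3 points)
- per-side spending function: 78.2% (difference 0.4 points)

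The observed hazard ratio just reaching significance at 120 events is exp(−2 × c2/sqrt(120)): 0.696 at 0.047, 0.697 at 0.048 and 0.698 at 0.049.

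**The case against.** The strongest reply is that the discrepancy lies in the third decimal and errs on the safe side. The purpose stated in the article is to conserve the overall type I error, and 0.0489 does so. With the final analysis at 120 events, the stated pair stays at or below 5% for interims tried from 40 events (0.0500) to 90 (0.0475). The interim level of 0.005 agrees with the classical boundary after rounding (0.0052). The third version, 0.0056/0.0478, would give exactly 0.005/0.047 if cut off at three decimals rather than rounded, so the pair may be a truncated form of a recognised boundary. All of this stands as to consequence. It does not make 0.047 the right figure: truncation is not correct rounding, and the article does not say that it was done.

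Three stronger readings are tempting, and the document does not support them.

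- A reader might infer that a final p between 0.047 and 0.048 would be wrongly called non-significant. A stricter level fixed in advance is a valid test, and failing it is the correct result under that rule.
- A reader might infer that the rule breaks if the looks do not fall at exactly 60 and 120 events. Once a spending function is named, recomputing levels at the actual counts is ordinary content for the statistical analysis plan, which the article says will be signed off before any analysis.
- A reader might object to a 95% confidence interval beside a 0.047 threshold. That is a common reporting convention and contradicts nothing, because the p value alone decides significance.

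Nor do the thresholds explain why power is about 78% rather than 80%. On the same formula, 120 events give 78.3% at a plain 5% level with no interim, so most of that gap lies in the event target.

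**Conclusion.** The point holds as a mismatch between a named method and a printed threshold, and no further. At 60 and 120 events and two-sided 5%, no O'Brien-Fleming version yields 0.047 by correct rounding. The interim value of 0.005 departs only from the spending-function versions (0.0031 or 0.0056), not from the classical boundary. The stated pair is valid and slightly conservative: overall type I error 4.9%, with 0.3 to 0.4 points of power given up. The trial's validity is not threatened. The point still deserves correction because it concerns the primary decision rule and leaves open which boundary governs.

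The result assumes the usual joint normal distribution of the two statistics with information proportional to events; the power figures also assume exponential PFS and proportional hazards. The source cited for the method was not available, but the calculation does not depend on it.

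**What to change.** Before any PFS look, name the exact boundary and restate both levels to match it in the Sample size and Primary endpoint analyses sections. Two choices:

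- **Classical O'Brien-Fleming boundary: 0.005 and 0.048.** Overall alpha is 0.0499 with these rounded values. The interim level does not change. The text should then call this the O'Brien-Fleming boundary and not a spending function.
- **O'Brien-Fleming-type spending function, 2.5% per side: 0.003 and 0.049.** Overall alpha is 0.0500 with these rounded values. This keeps the method now named. Its small downside is a stricter interim threshold, 0.003 in place of 0.005.

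Either choice costs wording only and leaves the sample size and event target unchanged. The timing matters because a threshold relaxed after unblinded PFS results have been seen would not be credible.

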### Secondary endpoint analyses

All secondary endpoint analyses comparing randomised participants will be assessed at the same time as the primary endpoint of PFS. The proportion of participants with undetectable MRD will be summarised (with 95% CIs) for participants randomised to consolidation therapy with obinutuzumab at 6 months post-randomisation and then at every time point at which MRD is assessed. CR, CRi and overall response (at least a PR) will be summarised (with 95% CIs) for participants randomised to consolidation therapy with obinutuzumab at 6 months post-randomisation and then at every time point at which response is assessed.

OS and treatment-free survival (TFS) (i.e., time from randomisation to next treatment or death) will both be assessed using Cox proportional hazards models to compare trials arms, adjusting for the minimisation factors. Kaplan-Meier curves, 95% CIs and median survival estimates will also be produced for both analyses by trial arm.

Participants who are registered and eligible but MRD-negative and so not randomised will also be followed for progression and death and will contribute to three secondary endpoint analyses. PFS, OS and duration of MRD negativity (i.e., time from end of most recent therapy for CLL to date of progression or death; date of death; or date of MRD relapse or death, respectively) will be assessed using Cox proportional hazards models to compare those who are MRD-negative at registration with those who become MRD-negative following consolidation therapy with obinutuzumab.

Occurrence and frequency of SUSARs, SARs, SAEs, AEoSI, AEs and treatment-related deaths will be summarised by trial arm and overall. In addition, all events will be summarised by maximum CTCAE grade reported and seriousness criteria, and all serious events will be summarised by Medical Dictionary for Regulatory Activities (MedDRA) System Organ Class, by trial arm and overall.

Mean QoL scores and 95% CIs, adjusted for the baseline score, will be calculated for all domains of the European Organisation for Research and Treatment of Cancer (EORTC) Core Quality of Life Questionnaire (QLQ-C30) and the CLL-specific module (EORTC QLQ-CLL16) for each trial arm and at each assessment time point and overall. Wilcoxon’s rank-sum tests will be used to compare the change in score for the trial arms from baseline to each time point.

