## Background

Chronic lymphocytic leukaemia (CLL) is the most common adult leukaemia. The CLL8 trial [1, 2] has shown that even though almost double the number of patients receiving fludarabine, cyclophosphamide and rituximab (FCR) achieved minimal residual disease (MRD) negativity (defined as <0.01% CLL cells) compared with those receiving fludarabine and cyclophosphamide, once low-level MRD was achieved, both arms showed the same prognostic significance. This indirectly implies that the depth of the remission may be more important than the type of treatment given to attain that remission. Attainment of MRD negativity has also been demonstrated as an independent predictor of overall survival (OS) and progression-free survival (PFS) even with a variety of different treatment approaches and regardless of the line of therapy [3].

The researchers in the U.K. National Cancer Research Institute (NCRI) CLL207 phase II trial [4] assessed whether participants with low levels of disease could attain MRD negativity following consolidation therapy with alemtuzumab. The results showed good efficacy, with 39 (83%) of 47 participants who were consolidated attaining MRD negativity. Overall, 38% remained MRD-negative in the peripheral blood 6 months after therapy, which may be the true MRD-negative population because this represents the time for redistribution of the disease among various compartments following antibody treatment. After a median follow-up of 44 months, the participants who were MRD-negative 6 months after treatment had a significantly increased PFS time compared with those participants who were MRD-positive, with a median PFS at 3 years of 94.4% in MRD-negative participants compared with 60.0% in MRD-positive participants (*p* = 0.004). However, alemtuzumab had a significant toxicity profile, with 22 serious adverse event (SAEs), 4 of which were clinically unacceptable (1 pneumocystis pneumonia, 1 parainfluenza-related death and 2 Epstein-Barr virus-related transformed diseases), reported in 17 (36.2%) participants.

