### Trial population

Patients who are eligible for the trial must be at least 18 years old, have previous confirmation of CLL, have undergone between one and three regimens of chemotherapy previously ending between 3 and 24 months before enrolment, have a peripheral B-cell count of <5 × 10^9^/L, have a response to the most recent chemotherapy treatment for CLL with PR, complete remission with incomplete marrow recovery (CRi) or CR. The patient must also be capable of giving written consent and have a World Health Organisation (WHO) performance status of 0 or 1.

Patients with any of the following characteristics are excluded from the trial: disease progression after response to last therapy, active infection, previous anaphylaxis to monoclonal antibodies, previous treatment with obinutuzumab, central nervous system involvement in CLL, mantle cell lymphoma, other severe concurrent diseases or mental disorders that could interfere with their ability to participate in the study (including moderate or worse cardiac diseases), known HIV positivity, positive serology for hepatitis B or C virus, persisting severe pancytopenia (neutrophils <0.5 × 10^9^/L or platelets <50 × 10^9^/L) or transfusion-dependent anaemia, vaccination with a live virus within 28 days, active haemolysis (patients with haemolysis controlled with prednisolone at a dose 10 mg or less per day can be entered into the trial), creatinine and bilirubin less than two times the upper limit of normal, previously treated with an allogeneic stem cell transplant, pregnant or lactating women, or women/men who are capable of conceiving children and who are unwilling to use appropriate medically approved contraception during and for 18 months after receiving treatment.

Once participants provide consent for the trial, peripheral blood will be tested for MRD. Patients who are MRD-negative will not be eligible for randomisation but will still be followed annually for MRD. Patients who are MRD-positive will have bone marrow and trephine samples tested centrally to confirm MRD level in the aspirate, a stratification factor for randomisation. To be randomised, participants must have an MRD-positive peripheral blood sample between 3 and 24 months since completing the last treatment for CLL and be confirmed as MRD-positive in the bone marrow. Participants must also have clinically and radiologically confirmed absence of lymphadenopathy (largest lymph node 1.5 cm or less in minimum diameter).

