### Intervention

Participants randomised to obinutuzumab consolidation will receive 100 mg of intravenous (IV) obinutuzumab on day 1 and 900 mg on day 2. The remaining course of treatment will be 1000 mg IV on days 8, 15, 22 (weekly), 36, 50, 64 and 78 (2-weekly). Participants randomised to no consolidation therapy will receive no treatment.

Participants will be assessed for their suitability for treatment within 1 week before each obinutuzumab treatment. At minimum, tests will be performed to ensure that dose delays or reductions are implemented and that concomitant medications are administered as per protocol.

Prior to medication, analgesic/antipyretic (equivalent to 1000 mg of paracetamol) will be administered before each treatment. Antihistamine (equivalent to 10 mg of cetirizine) will be administered prior to days 1 and 2 of treatment and for remaining treatments for participants with an infusion-related reaction (IRR) (Common Terminology Criteria for Adverse Events [CTCAE] [13] grade 1 or higher) to the previous infusion. Corticosteroid infusion (equivalent to 100 mg of prednisolone) will be administered for days 1 and 2 and for participants with a grade 3 IRR with the previous infusion or participants with a lymphocyte count >25 × 10^9^/L before treatment. No concomitant cytotoxic agents, radiotherapy or vaccination with live viruses should be given.

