### Follow-up

A formal assessment of disease response will be made 6 months post-randomisation (or at least 2 months after last treatment if treatment has been delayed). As shown in Figs. 2 and 3, this will require a physical examination and local laboratory tests; the collection of blood, bone marrow aspirate and trephine samples (for participants randomised to treatment, and trephine only where clinically indicated); CT scan (where clinically indicated); and assessment of QoL.

Follow-up visits to assess ongoing disease response and survival will be made every 3 months between 9 and 36 months post-randomisation. Participants who are MRD-negative post-consolidation treatment will also have blood collected at 12, 24, 36 and 48 months post-randomisation. All participants will be followed annually for survival until death. MRD blood assessments will end once a participant becomes MRD-positive.

All trial MRD testing will be carried out centrally by the Haematological Malignancy Diagnostic Service at Leeds Teaching Hospitals National Health Service (NHS) Trust using the harmonised European Research Initiative on CLL method [14] to ensure standardisation of reporting. Participants who are MRD-negative at baseline will have blood collected for MRD analysis at 12, 24 and 36 months post-registration. No further samples are collected if the participant becomes MRD-positive.

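### The comparison of the two MRD-negative groups has no common landmark: status is judged at different times after the last dose, and the direction of the resulting bias cannot be fixed

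*Protocol article*

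**What the plan says.** All references are to the protocol article.

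- **The comparison.** Secondary endpoint analyses plans Cox models to "compare those who are MRD-negative at registration with those who become MRD-negative following consolidation therapy with obinutuzumab", for PFS, OS and duration of MRD negativity. The clock for PFS is "time from end of most recent therapy for CLL to date of progression or death"; OS and duration of negativity share that origin. The section does not say whether, for consolidated participants, this means the end of chemotherapy or of obinutuzumab.
- **Registrants.** Under Trial population, participants must "have undergone between one and three regimens of chemotherapy previously ending between 3 and 24 months before enrolment". Blood is tested for MRD after consent, and those who are negative are followed without randomisation.
- **Consolidated participants.** Under Intervention, the dosing schedule ends with "1000 mg IV on days 8, 15, 22 (weekly), 36, 50, 64 and 78 (2-weekly"). Under Follow-up, the formal assessment falls at "6 months post-randomisation (or at least 2 months after last treatment if treatment has been delayed"). After that, "Participants who are MRD-negative post-consolidation treatment will also have blood collected at 12, 24, 36 and 48 months post-randomisation".
- **Why timing matters.** The Background reports an alemtuzumab consolidation trial in which 39 of 47 participants (83%) became MRD-negative and 38% were still negative in blood at the 6-month point. Of that smaller group it says: "which may be the true MRD-negative population because this represents the time for redistribution of the disease among various compartments following antibody treatment". Three-year PFS by that 6-month status was 94.4% for negatives and 60.0% for positives.

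**The concern.** The comparison asks whether negativity reached by consolidation is worth as much as negativity reached by chemotherapy alone. To answer that, membership of the two groups should mean the same thing. Here the consolidated group is classified soon after an antibody course, and most registrants probably later after their therapy. If some early negatives are transient, they may collect in the consolidated group and lower its PFS and duration of negativity, even when durable negatives do equally well in both.

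There is a second problem. The outcome clock starts before classification, so each group carries a stretch in which no event can have occurred, and the stretch differs between groups. Without a shared landmark, the hazard ratio mixes three things: the value of negativity, the share of transient negatives, and guaranteed event-free time.

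**Working it through.** **1. Time from last dose to classification**

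- Consolidated, on schedule, dosing from the day of randomisation: (182.6 − 78)/30.44 = 3.44 months. A start 2 or 4 weeks after randomisation (assumed) shortens this to about 3.0 or 2.6 months. After delayed treatment the stated minimum is 2 months.
- Registrants: 3 to 24 months. If entry is uniform over that window (assumed), 3/21 = 14% are classified before 6 months.

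**2. The Background figures**

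39/47 = 83.0%. The 38% implies 18/47 = 38.3%. If those 18 are among the 39, then (39 − 18)/39 = 54% of those who became negative were no longer negative at 6 months.

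**3. Effect of transient negatives alone (illustration)**

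Assumptions, none of them in the article:
- the fall from 83% to 38% is log-linear over 6 months and carries over to obinutuzumab;
- nobody negative at 6 months or later is transient;
- registrants enter uniformly over 3 to 24 months;
- transient negatives have 60.0% and durable negatives 94.4% three-year PFS.

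The retained share over 6 months is 0.38/0.83 = 0.458. The transient share at t months is f(t) = 1 − 0.458^((6 − t)/6). Three-year PFS is (1 − f) × 0.944 + f × 0.600. The hazard ratio (HR) is the ratio of the logs of the two PFS values.

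| Group | f | 3-year PFS | HR v registrants |
|---|---|---|---|
| Registrants, averaged over 3–24 months | 0.025 | 0.936 | – |
| Consolidated, 3.44 months | 0.284 | 0.846 | 2.5 |
| Consolidated, all at 2 months | 0.406 | 0.804 | 3.3 |
| Consolidated, 10% transient | 0.10 | 0.910 | 1.4 |

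The 2-month row would need every participant to be delayed, so 1.4 to 2.5 is the more reasonable range.

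**4. Sensitivity to registrants' entry times**

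If all registrants enter at 3 to 6 months, their average f is 0.172 and their PFS 0.885. The HR is then ln(0.846)/ln(0.885) = about 1.4 in place of 2.5, and ln(0.910)/ln(0.885) = about 0.8 in place of 1.4. The sign can reverse.

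**5. Effect of guaranteed event-free time alone**

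Simulation with equal hazards in both groups (medians of 24, 36 and 60 months), uniform 3–24 month entry and 48 months of follow-up:

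| Origin for consolidated group | Guaranteed time: consolidated v registrants | Naive HR |
|---|---|---|
| End of chemotherapy | 9–30 v 3–24 months | 0.79–0.87 |
| End of obinutuzumab | about 3.5 v 3–24 months | 1.35–1.50 |

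Delayed entry at classification brings all of these back to about 1.0.

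**6. Both mechanisms together**

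Using the 94.4% and 60.0% rates:

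| Transient share, consolidated v registrants | Chemotherapy origin | Obinutuzumab origin |
|---|---|---|
| 28% v 2.5% | about 2.1 | about 3.2 |
| 10% v 2.5% | about 1.2 | about 1.7 |
| 10% v 10% | about 0.9 | about 1.2 |

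**The case against.** A reader might infer that the protocol treats 6-month negativity as the true kind and that the comparison will therefore make consolidated participants look worse. The document supports neither. The Background wording is tentative, concerns alemtuzumab and peripheral blood, and is not a definition for this trial. The net direction depends on an ambiguous origin and on unknown transient shares. Elsewhere (Randomisation, the staging factor) the most recent CLL therapy means the pre-trial therapy. That leans towards the chemotherapy origin, which by itself favours the consolidated group.

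Further points against, most of which stand:

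- **Month 6 is inferred.** The comparison does not say when becoming negative is judged, and a condensed article may leave this to the analysis plan. But month 6 is the formal response assessment, and later MRD blood is scheduled only for those already negative, so no other entry time is evident. The origin that is stated precedes classification in any case.
- **The PFS inputs are rough.** The 60.0% belongs to everyone positive at 6 months, including the 47 − 39 = 8 who never became negative. The 83% is attainment, not status on the day of the last dose.
- **Compartments differ.** Registrants are classified on blood alone, while consolidated participants also give marrow at month 6. If marrow counts, their definition may be the stricter one.
- **Less durable negativity may be a real finding.** Excluding early relapsers could hide it. This is a fair limit on any landmark and has to be met by reporting them.
- **A landmark is not perfectly symmetric.** Consolidated participants must be negative at months 6 and 12, most registrants only once, and times since therapy still differ.

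**Conclusion.** The point holds as a design weakness in a secondary, non-randomised comparison. The groups are classified at about 2 to 3.4 months and at 3 to 24 months after last therapy, with no common landmark and with a clock that starts before classification in both.

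Transient negatives alone would tilt the result against consolidation, with an illustrative HR of about 1.4 to 2.5. That range rests on carrying alemtuzumab blood data over to obinutuzumab and on uniform registrant entry. If registrants enter early, the HR can fall to about 0.8. Guaranteed event-free time alone gives about 0.79 to 0.87 or 1.35 to 1.50, depending on the origin. These are scenarios, not estimates. What can be said is that the comparison as written can be materially biased and that its net direction is not established. The primary PFS analysis of the randomised arms is not touched.

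**What to change.** As the main version of this secondary comparison, specify a landmark analysis:

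1. Define both groups by a negative peripheral blood result at least 6 months after the last dose of the relevant therapy. For consolidated participants use the month-12 blood, which on schedule falls (365.25 − 78)/30.44 = 9.4 months after the last dose. For registrants use the registration sample if taken at 6 months or later, otherwise the 12-month sample.
2. Start follow-up for all three outcomes at that sample.
3. Account for the remaining differences in time since last therapy, for example by adjustment.
4. Keep the current grouping as a sensitivity analysis, stating which therapy's end is the origin for the consolidated group.
5. Report how many in each group relapse or progress before the landmark, so that less durable negativity stays visible.

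Under the assumptions of the illustration, transient negatives have turned positive before the landmark and both groups then contain only durable negatives, so the spurious HR disappears. Outside those assumptions the gain is smaller.

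The cost is analysis wording only, because every sample is already scheduled under Follow-up. The downside is smaller groups, and conclusions that apply only to participants still negative at the landmark.
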